**Analysis**

Analysis of this study will be conducted using intention to treat. Participants randomized to the *Zindagi* SMS group will be considered a part of that group for analysis, regardless of whether they used the SMS system or not.

*Primary Outcome*

The primary outcome for this study is clinically-recorded treatment outcomes. Treatment outcomes for TB patients include cure, treatment complete, treatment failure, died, transfer out, or default. These are reported by TB clinics to the National TB Control Program on all their patients on treatment. We will look at treatment success rates of patients in our study, as recorded by their TB clinics, to compare the means for these outcomes between our intervention and control groups.

*Secondary Outcomes*

There are a number of secondary outcomes for this study:

Medication adherence: Medication adherence will be measured through urinalysis tests and self-reports by participants on whether they took their medication in the past 24 hours. This data will be collected during unannounced midline visits.

Phyical fitness and mobility: Physical fitness will be measured through questionnaires conducted with participants during household visits each month that they are on treatment. The physical fitness index will look at the self-reported ability of respondents to complete certain tasks.

Pyschological impacts: In order to cause of the psychological impacts of the system, the investigators will look at participants’ perceptions of the likelihood of being cured, how healthy they feel on a given day, and how supported they feel.

Sputum conversion: Sputum samples will be collected and we will look at the difference in when sputum conversion occurs between the *Zindagi SMS* and control groups.

*Sub-group Analysis*

In order to test the differential effects of the intervention on various sub-groups, we will be conducting the following sub-group analysis.

- Gender : Women in Pakistan often have restrictions on their mobility. Therefore, an SMS reminder system may be more beneficial to them, as they receive reminders in the comfort of their homes. Women are also more likely to be at home, thereby enabling greater access to the owner of the mobile phone (if it is not the patient herself), as they will be home whenever the owner of the mobile phone is at home. Alternatively, women may be less comfortable with technology and therefore there may be less likely to use the system. Moreover, TB stigma is more prevalent in women, especially young women, and so they may benefit from a remote system that sends messages to them at home.
- Vulnerable Populations: We will be looking at the impact of the system on vulnerable populations. In order to look at whether a participant is vulnerable, we will be looking at a variety of variables related to education, gender, and socioeconomic status. Less vulnerable respondents may be more likely to benefit from the intervention, as they may have better health-seeking behaviour and so a reminder system may result in them acting on the reminders. Alternatively, there may be more of an impact on those of a lower socio-economic group, as they may have worse health-seeking behaviour to begin with and, therefore, the system may have a greater impact on them. We will construct a family of indicators that measure socioeconomic status and test for a heterogeneous treatment effect by socioeconomic status.
- Access to a Mobile Phone: We will be looking at the impact of the system based on participants’ relative access to a mobile phones. The extent of access to mobile phones will be determined by ownership of the phone and familiarity with SMS at baseline. We will also look at factors such as literacy of the patient, literacy of their household members, and the language they use to SMS. Increased access to the mobile phone may increase compliance, because the patient will personally be able to see the messages, which could result in improved compliance. Alternatively, patients that have less personal access to the mobile phone may be reminded family members who have greater access, which could increase their compliance, as they will be monitored by the owner of the mobile phone.
- Quality of Care: We will also be looking at the quality of care received by patients as a sub-group to analyze. Quality of care will be determined by the clinic the patient receives treatment from, whether or not they have a treatment supporter, and whether there is anyone who reminds them to take their medication. We hypothesize that the lower the quality of care, the more impact the system will have, as it will enhance the quality of their care through reminders. However, if the quality of care is so poor that there is a lack of availability of the medication, then this may result in a reduced impact of the system, as it cannot over-ride issues of a lack of availability of medication.
- People likely to respond to Interactive Reminders: We will also use those who are more likely to respond to SMS reminders as a sub-group to analyze. It may be that those who respond more get a greater benefit from the intervention. Thus, we will look at various socio-demographic variables such as gender, age, socio-economic status, literacy, education, and education of other family members, to see whether these are have a significant correlation with response rates for people in the Interactive Reminders arm. Once that is determined, we will examine the impact of Interactive Reminders on this sub-group.

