**Research Methods**

This study is a randomized control trial that will take place in Karachi, Pakistan. Participants will be recruited through TB clinics throughout the city.

*Participant Inclusion/Exclusion Criteria*

The sample for this study will be drawn from newly diagnosed TB patients with sputum or bacteriologically-positive drug-susceptible TB who are at least 15 years of age in Karachi, Pakistan. Study participants will be required to own a cell phone or have access to one. To reduce spillover effects, patients will be excluded from the study if another household member is already participating. Finally, to enable follow up surveys, participants will have to intend to reside in Karachi throughout their treatment period.

*Recruitment, Randomization, and Data Collection*

When a clinic diagnoses a new patient with tuberculosis, the study’s clinic representative will inform the participant about the study. If a patient meets the eligibility criteria, they will be read an oral informed consent form and will be asked to participate in the study. Emphasis will be placed on explaining that they can refuse to take part in the study without there being any effect on the standard treatment provided to them by the clinic. They will also be informed that participation will require several interviews over the course of the patient’s treatment. Recruitment of minors (below the age of 18) will require the patient's asset as well as informed oral consent from the patient's parent/guardian.

If a participant consents to participate in the study, clinic representatives will then complete a brief enrolment form, including the patient’s name, age, sex, clinic location, as well as other contact information. Random assignment in this study will occur on a rolling basis as new patients are diagnosed with tuberculosis. Patients will be randomized through an electronic randomization process at the time of enrolment, to prevent personal bias from contaminating the randomization process. Patients will be randomized into either the control arm or the *Zindagi SMS* arm of the study using programs on the clinic representatives' mobile phones. Participants will be informed of their randomization status but it will not be shared with their treating clinics by the study representatives.

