
We calculated a minimum sample size of 1,094 per arm to detect an effect size of 5%, from a treatment completion rate of 75% to 80%.

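### The primary comparison as described does not use clinic, age and sex from the enrolment form; naming them as adjustment variables would probably add a small amount of power at little cost

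*Protocol*

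**What the plan says.** Under Analysis, Primary Outcome, success rates taken from clinic records are used "to compare the means for these outcomes between our intervention and control groups". The population is fixed by "Analysis of this study will be conducted using intention to treat". No test, model or covariate is named.

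Under Research Methods, "Participants will be recruited through TB clinics throughout the city", and the enrolment form takes the patient's "name, age, sex, clinic location, as well as other contact information". The form is described first and electronic randomisation at enrolment second. Nothing is said about stratifying by clinic, age or sex.

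Under Sample Size, "We calculated a minimum sample size of 1,094 per arm" is given "to detect an effect size of 5%, from a treatment completion rate of 75% to 80"%, with no significance level, power or covariate.

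Under Sub-group Analysis, Quality of Care, the treating clinic is one of three markers of the quality of care a patient receives.

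**The concern.** The primary outcome is assigned by the patient's own clinic and retrieved from that clinic's register. Differences between clinics in care or record-keeping would therefore show up in the endpoint, and the protocol itself expects clinics to differ in quality of care. Clinic, age and sex are known for everyone, so adjusting for them drops no one and fits intention to treat. A comparison of means that ignores them leaves whatever variance they explain in the error term. What is at stake is a modest amount of precision. Validity is not in question.

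**Working it through.** **Inputs.** Success 75% and 80%, and 1,094 per arm, from the Protocol's Sample Size section (its completion rate is taken as the success rate). Two-sided 5% and 80% power are inferred. The share of variance explained by clinic, age and sex (R²) is not given, so it is assumed over a range.

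**1. Reproduce the plan's figure.** With pooled rate 0.775:

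n = [1.960·√(2·0.775·0.225) + 0.8416·√(0.75·0.25 + 0.80·0.20)]² / 0.05²
= [1.960·√0.34875 + 0.8416·√0.3475]² / 0.0025
= (1.1575 + 0.4961)² / 0.0025 = 1,093.7, rounded up to **1,094**.

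Other settings miss: 862 (one-sided, 80% power), 1,134 (continuity correction), 1,251 (85% power) and 1,464 (90% power). The sizing therefore matches a two-proportion test without covariates, with power 80.0%.

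**2. Effect of adjustment.** Residual variance is multiplied by (1 − R²), so effective n is 1,094/(1 − R²), and

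power = Φ[(0.05·√(effective n) − 1.960·√0.34875) / √0.3475].

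For R² = 0.05: effective n = 1,151.6, and (1.6968 − 1.1575)/0.5895 = 0.915, so power is 82.0%.

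| Assumed R² | Power at 1,094 per arm | n per arm for 80% power | Saving per arm |
|---|---|---|---|
| 0 | 80.0% | 1,094 | 0 |
| 0.02 | 80.8% | 1,073 | 21 |
| 0.03 | 81.2% | 1,062 | 32 |
| 0.05 | 82.0% | 1,040 | 54 |
| 0.10 | 84.0% | 985 | 109 |

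**3. Which R² is plausible.** The total variance of a success indicator is 0.775·0.225 = 0.1744. A between-clinic standard deviation (SD) of 5 points gives R² = 0.05²/0.1744 = 0.014. An SD of 10 points gives 0.057, and 15 points gives 0.129. A 10-point difference between the sexes, in equal numbers, gives 0.25·0.10²/0.1744 = 0.014.

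**4. Check by simulation, including the cost of fitting clinic terms.** 2,188 patients, 30 clinics (assumed), simple randomisation, linear model with robust standard errors, 2,000 replicates. Mean standard errors of the difference:

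| Scenario | Unadjusted | Adjusted | Change in variance |
|---|---|---|---|
| Covariates not prognostic | 0.01783 | 0.01796 | +1.4% |
| Clinic SD 5 points, modest age and sex effects | 0.01783 | 0.01775 | −0.8% |
| Clinic SD 10 points, modest age and sex effects | 0.01783 | 0.01740 | −4.8% |
| Clinic SD 15 points, stronger age and sex effects | 0.01798 | 0.01697 | −11.0% |

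In the step 2 formula, reductions of 0.8% and 4.8% give 80.3% and 81.9% power. The non-prognostic case has a standard error 0.7% larger (0.01796/0.01783 = 1.007), which costs about half a power point.

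**5. Does the sizing already contain clinic variation?** Yes. Patients are randomised individually, and total variance splits into within-clinic and between-clinic parts. With a clinic SD of 10 points, 0.1744 = 0.1644 + 0.0100. The formula in step 1 uses the whole binomial variance, so the between-clinic part is already counted.

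**The case against.** The strongest objection is that this is silence, not error. A comparison of arm means can be made with or without covariates, the protocol rules out neither, and the covariate set is commonly left to a statistical analysis plan, which is not shown here. That stands in part: a reader might infer that the protocol declares an unadjusted analysis, but the word does not appear. The reading is reasonable because the sentence names no covariate and the sizing matches a covariate-free test, but it remains an inference.

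Other inferences go further than the documents allow:

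- **That the sizing lacks the reserve to absorb clinic variation or chance imbalance in clinic mix.** Step 5 shows that clinic variation is already in the variance used. Chance imbalance is part of the sampling error that the ordinary standard error measures. Under the sizing assumptions there is nothing further to absorb.
- **That randomisation is unstratified.** The protocol does not say how the allocation lists are built.
- **That clinic is a strong predictor.** The Quality of Care text is a sub-group hypothesis and gives no success rates by clinic.
- **That the precision is free.** The gain may be nil or slightly negative. The number and size of clinics are not given, and a pooling rule for small clinics is needed; left open, it would add an analyst's choice to the primary comparison.
- **That the covariates are stated to precede randomisation.** This follows from the order of the text. Age, sex and clinic location at enrolment could hardly depend on arm in any case.

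**Conclusion.** A low-severity efficiency point, not a defect. The comparison as described is valid under randomisation and delivers its planned power (80%, inferred). Adjusting for clinic, age and sex would add about 0 to 4 power points for an assumed R² of 0 to 0.10. The likely gain is about 1 to 2 points if clinics differ moderately, with the upper figure needing a between-clinic SD near 10 points and little gained at 5. The downside is a standard error about 0.7% larger if none of the three is prognostic. These sizes rest on the inferred 5% level and 80% power, on R² values the protocol does not supply, and, for the simulation, on 30 clinics. The point lapses if a separate analysis plan already specifies the adjustment.

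**What to change.** In the Protocol, Analysis, Primary Outcome, state that:

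- the primary estimate is the risk difference from a linear regression of treatment success on arm, adjusted for clinic, age and sex as recorded on the enrolment form, with robust standard errors;
- small clinics are pooled by a rule fixed before any outcome data by arm are seen;
- the raw difference in success rates is reported as a supporting analysis;
- items from the Baseline survey are not used for adjustment, because that survey is a voluntary visit made after allocation.

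The cost is a short addition to the text and a decision on the pooling rule. No new data are needed, and neither the sample size nor the risk-difference scale changes. If a separate analysis plan already contains this, a cross-reference is enough.

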**Background and Rationale**

In Karachi, Pakistan, the incidence of TB is believed to be particularly high, with13,332 patients registered under the National TB Control Programme (NTP) in 2007. Increasingly, the problem of non-compliance is leading to the emergence of multi-drug resistant TB (MDRTB), a form of TB that is more expensive and difficult to treat. Of 7,185 new pulmonary cases studied in Karachi in 2006, 12% were reported to have defaulted on treatment. The system currently recommended by the World Health Organization (WHO) for tackling the problem of non-compliance is Directly Observed Therapy Short-Course (DOTS), which involves on-site, in-person monitoring of compliance with medication. DOTS programmes in Karachi use health workers, health clinic staff, or treatment supporters, who are usually family members, as monitors. However, there is no way of verifying whether and to what extent patients are complying with their drug regimen.

Remote reminders free patients from their dependence on unreliable health workers. IRD is conducting a randomized control trial to gauge the impact of the *Zindagi SMS* system on treatment outcomes for patients with drug-susceptible TB.

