If the patient is selected into *Zindagi SMS,* the clinical representative will explain the program to the patient, provide him/her with an informational brochure, and provide him/her with a number to call for assistance.

Data collection for the study will occur in three stages for participants in both the *Zindagi SMS* and control groups: Baseline, Midline Surveys, and Endline surveys. The three stages will occur over the standard course of treatment for tuberculosis. The Baseline survey will occur during Month 1 of treatment, Midline data collection will occur on a monthly basis during Month 2 through to Month 7 of treatment (or Month 5 of treatment for participants on the six-month regimen), and the Endline survey will occur after the completion of the expected treatment period. Sputum samples will be attempted from patients after their first, second, fifth and sixth or seventh months of treatment. Each stage of data collection will be voluntary, include informed consent, and be conducted in the patient’s home or in private to ensure confidentiality. All survey questions will be extensively field-tested prior to use in the study in order to be sure that all material covered is culturally sensitive and respectful of local beliefs.

Baseline Survey: Survey enumerators will attempt to visit newly diagnosed TB patients within a week of diagnosis. The baseline survey will collect background information on socio-demographic factors as well as other health conditions.

Midline Surveys: Compliance checks will be attempted every month between Month 2 and Month 7 (or Month 5 for those on an six month regimen) after enrolment. During these months, research staff will conduct unannounced visits to ask participants whether they took their medication in the past 24 hours, and a range on questions about their treatment, health, mobile phone usage, and employment. Urinalysis tests will also be used to objectively gauge compliance.

Endline Survey: After the end of the expected treatment period, enumerators will revisit study participants to conduct a final endline survey. The endline survey will collect information on their health, treatment, as well as attitudes toward compliance with drug regimes.

Clinical outcomes form: Using the patient's District TB number, clinically reported treatment outcomes will be retrieved through the clinic registers. This will enable use clinically reported results to compare outcomes across treatment and control groups.

*Sample Size*

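### Tying the physical fitness questionnaire to months on treatment, read literally, ends measurement at a post-randomisation event that the SMS system is meant to change

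*Protocol*

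**What the plan says.** Three parts of the protocol bear on this point.

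- **Analysis, Secondary Outcomes (physical fitness and mobility):** "Physical fitness will be measured through questionnaires conducted with participants during household visits each month that they are on treatment". The index is built from self-reported ability to carry out certain tasks.
- **Analysis, opening paragraph:** "Analysis of this study will be conducted using intention to treat". The only elaboration is that participants randomised to the SMS group stay in it for analysis "regardless of whether they used the SMS system or not".
- **Research Methods, Recruitment, Randomization, and Data Collection:** the midline paragraph says "Compliance checks will be attempted every month between Month 2 and Month 7 (or Month 5 for those on an six month regimen) after enrolment". At these unannounced visits staff also ask "a range on questions about their treatment, health, mobile phone usage, and employment". Then: "After the end of the expected treatment period, enumerators will revisit study participants to conduct a final endline survey".

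Default is one of the recorded treatment outcomes from which the primary outcome is formed. The Background says that of 7,185 new pulmonary cases studied in Karachi in 2006, "12% were reported to have defaulted on treatment".

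**The concern.** The fitness sentence makes measurement depend on the participant's own status in a given month. A participant who stops in Month 3 would, on that wording, give no fitness data afterwards. Whether someone is still on treatment is decided after randomisation, and the reminders exist to influence it. Restricting measurement to people still on treatment therefore compares two groups selected by a process that may differ between arms, and the protection given by randomisation is lost.

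The likely direction is unfavourable to the intervention. If reminders keep some marginal patients on treatment, and those patients are less fit than the rest, they enter the SMS average while their control counterparts drop out of view.

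This is a rule about what data are collected. An analysis plan can say how to handle missing values, but it cannot recover questionnaires that were never administered.

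**Working it through.** **1. The passages side by side.**

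| Item | Fitness sentence (Analysis) | Visit schedule (Research Methods) |
|---|---|---|
| Window | months in which the participant is on treatment | Month 2 to Month 7 (or 5), counted from enrolment; endline after the expected treatment period |
| Does it end at default? | yes, if read literally | no such rule stated |
| Fitness index named? | yes | no; health questions at midline and endline only |

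Field staff could follow either text for a patient who has stopped treatment, and would collect different data.

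**2. The plan's own figure.** The Sample Size paragraph gives 1,094 per arm for completion of 75% against 80%. Assuming two-sided alpha 0.05, 80% power, equal allocation and pooled variance (none of them stated):

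n = [1.960 × √(2 × 0.775 × 0.225) + 0.8416 × √(0.75 × 0.25 + 0.80 × 0.20)]² / 0.05² = (1.1575 + 0.4961)² / 0.0025 ≈ 1,094.

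The figure reproduces. It concerns the primary outcome and is used here only for the number per arm.

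**3. How many participants could be affected.**

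- Non-completion at the planning rates: 1,094 × 0.25 = 273.5 (control) and 1,094 × 0.20 = 218.8 (SMS). These counts include deaths and transfers as well as default, and are reached only by the end of the course.
- Default at the background rate: 1,094 × 0.12 = 131.3 per arm.

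**4. Direction and size of the selection.** The protocol gives no fitness means, so these are assumptions in SD units. Split participants into 75% who complete in either arm (mean 0), 5% who complete only with SMS (mean *a* on treatment, *b* off it) and 20% who complete in neither arm (mean *b*). Treat non-completers as off treatment, and let SMS act only by keeping the 5% on treatment.

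- All-randomised difference = 0.05 × (*a* − *b*)
- On-treatment difference = (0.05 × *a*) / 0.80 − 0

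| *a* | *b* | All randomised | On treatment only | Shift |
|---|---|---|---|---|
| 0 | −0.5 | +0.025 | 0.000 | −0.025 |
| −0.3 | −0.5 | +0.010 | −0.019 | −0.029 |
| −0.3 | −1.0 | +0.035 | −0.019 | −0.054 |
| −0.5 | −1.0 | +0.025 | −0.031 | −0.056 |

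In the first row the effect disappears; in the other three its sign changes.

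**5. Scale.** With SD 1 and 1,094 per arm at one visit, the standard error of a difference in means is √(2 / 1,094) = 0.043. The shifts are about 0.6 to 1.3 standard errors (0.025 / 0.043 to 0.056 / 0.043), and the true differences in this illustration are all below one standard error.

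**The case against.** The strongest reply is that the phrase is loose wording for the treatment course. The data-collection section itself first labels the midline months as months of treatment and then describes the same visits as months after enrolment, so the two labels look interchangeable. Nothing ends visits at default, and endline is timed by the expected rather than the actual treatment period. This reply stands as far as it goes: the intent may well have been monthly visits throughout the expected course. It does not remove the difficulty. The fitness sentence is the only outcome description in the Analysis section tied to being on treatment, and the endline paragraph does not name the fitness index, so endline cannot be assumed to fill the gap.

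A reader might go further and infer three things that the protocol does not support.

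- *That it contradicts its intention-to-treat rule.* The rule as spelled out concerns group membership regardless of use of the SMS system, and no passage excludes defaulters from analysis. Handling of missed visits and deaths may also be set out in an analysis plan that is not shown.
- *That adherence and psychological outcomes carry the same restriction.* Adherence is tied to the unannounced midline visits without that qualifier, and the psychological item has none either.
- *That a serious reversal of the trial's findings is likely.* The reversals above depend on chosen fitness means, and the shifts are small.

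**Conclusion.** The point holds in limited form. As written, the fitness sentence allows measurement to stop when treatment stops, and it sits badly with a visit schedule that runs from enrolment. If followed literally, fitness data would be lost in a way related to both arm and prognosis. That undermines the intention-to-treat comparison for this one secondary outcome.

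The size is probably modest: a shift of about 0.03 to 0.06 SD. This rests on assumed fitness means, on the planning completion rates, on treating non-completers as off treatment, and on an effect acting only through retention. At earlier visits fewer participants will have stopped, so the shift there should be smaller. The shift is nonetheless at least as large as the effect being estimated in every scenario shown, which is why the wording deserves correction. The primary outcome and the sample size are not affected.

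**What to change.** Replace the on-treatment qualifier in the fitness sentence with wording to this effect: the fitness questionnaire is attempted at every scheduled monthly household visit of the expected treatment period, for all randomised participants, whether or not they are still taking treatment, and is analysed by randomised arm.

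The adherence and psychological items need no rewording, only confirmation that they follow the visit schedule in the data-collection section.

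The cost is one sentence in the protocol and some added effort to trace participants who have stopped treatment. The visits are already scheduled, and clinical care does not change.

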**The *Zindagi SMS* System**

The *Zindagi SMS* reminder system is a two-way medication reminder system for people with drug-susceptible tuberculosis. Participants are sent daily medication reminder SMS messages and are asked to respond with an SMS to indicate that they have taken their medication for the day. If the system does not receive a response within two hours, a second reminder is sent. If the system does not receive a response for another two hours, a third and final reminder is sent. Participants who are non-responsive for a week are followed up with a phone call.

Participants are offered PKR 60 per month, as compensation for the cost of sending SMS messages.

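### Predictors of SMS reply are chosen in the intervention arm and the effect is then examined in the same patients, which can tilt the likely-responder contrast towards benefit

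*Protocol*

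**What the plan says.** The last item under Sub-group Analysis (Protocol, Analysis) sets out two steps. The first takes "various socio-demographic variables such as gender, age, socio-economic status, literacy, education, and education of other family members" and checks them "to see whether these are have a significant correlation with response rates for people in the Interactive Reminders arm". The second reads: "Once that is determined, we will examine the impact of Interactive Reminders on this sub-group". No separate sample, cut-off or model is named.

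Three other statements bear on this:

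- The Zindagi SMS System: patients "are asked to respond with an SMS to indicate that they have taken their medication for the day". A reply is therefore a self-report of adherence made after randomisation, and only the intervention arm can produce it.
- Research Methods: "The baseline survey will collect background information on socio-demographic factors as well as other health conditions". The same section says that the survey stages cover both arms, so the candidate traits are available for controls too.
- Research Methods: "Patients will be randomized into either the control arm or the *Zindagi SMS* arm of the study". These are the only two arms.

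**The concern.** Reply rate is plausibly tied to treatment outcome, because it reports doses taken and because a patient who defaults or dies stops replying. Suppose that, by chance, some trait goes with good outcome among the SMS patients. The same trait will then tend to go with higher reply rates in that arm, and will be more likely to be picked as a marker of likely response. When the effect is examined in a subgroup that includes those same patients, the chance association counts towards the SMS arm. Controls have no replies and so no matching step.

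The resulting error has one direction: it makes likely responders appear to gain more and unlikely responders less. At stake is one subgroup conclusion, that the system works best in an identifiable type of patient.

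**Working it through.** **Planned size.** With p1 = 0.75, p2 = 0.80, two-sided 5% and 80% power (the last two are assumed, since the Protocol does not state them):

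n = [1.96·√(2·0.775·0.225) + 0.8416·√(0.75·0.25 + 0.80·0.20)]² / 0.05² = 1,093.7, so 1,094 per arm. This matches the Sample Size statement, and N = 1,094 per arm is used below.

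**Set-up.** There is no treatment effect for anyone and success is 75% in both arms. Reply rate is regressed on k baseline variables in the SMS arm, both arms are scored, and the score is split at its median. The quantity of interest is the treatment effect in the high group minus that in the low group, whose true value is 0. The linear score and median split are assumptions.

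**Approximate formula when the variables do not predict replies.** By chance the fitted score correlates about √(k/N) with reply rate in the SMS arm. It therefore correlates about ρ·√(k/N) with success, where ρ is the correlation of reply rate with success. A median split turns this into

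bias ≈ 2·√(2/π)·SD(y)·ρ·√(k/N) = 1.596·0.433·ρ·√(k/N) = 0.691·ρ·√(k/N).

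The contrast uses four cells of about 547, so SE = √(4·0.1875/547) = 3.70 points. With δ = bias/SE, the false-positive rate is about Φ(−1.96+δ) + Φ(−1.96−δ).

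**Assumed values of ρ.**

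- Model A: an unmeasured trait drives replies and success, with latent correlation 0.3 or 0.5. Dichotomising success at 75% multiplies this by 0.3178/0.433 = 0.734, giving ρ = 0.220 or 0.367.
- Model B: mean reply rate is 0.5 in successes and 0.2 in others, with further spread of SD 0.2. Then ρ = √[0.3²·0.1875/(0.3²·0.1875 + 0.04)] = 0.545.

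| k | ρ | √(k/N) | bias, points | δ | false positives |
|---|---|---|---|---|---|
| 6 | 0.220 | 0.0741 | +1.1 | 0.30 | 6% |
| 6 | 0.367 | 0.0741 | +1.9 | 0.51 | 8% |
| 6 | 0.545 | 0.0741 | +2.8 | 0.75 | 12% |
| 20 | 0.545 | 0.1352 | +5.1 | 1.38 | 28% |
| 30 | 0.220 | 0.1656 | +2.5 | 0.68 | 10% |
| 30 | 0.367 | 0.1656 | +4.2 | 1.14 | 21% |

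**Adding the significance screen.** A useless variable that passes at 5% has mean |z| = 2·0.0584/0.05 = 2.34. Under Model B its correlation with success is 0.545·2.34/√1,094 = 0.0386. For one yes/no variable split half and half, the bias is 2·0.0386·0.433 = 3.3 points. Then δ = 0.90 and the false-positive rate is about 15%.

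**Simulation at 1,094 per arm, fitted and tested on the same SMS patients.**

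| Case | Model A | Model B |
|---|---|---|
| 6 variables, no prediction of replies | +1.2 to +1.8; 6.5–8.7% | +2.6 to +2.9; 10–11% |
| 6 variables, explaining 5–10% (A) or 2–10% (B) of reply variance | 0.0 to +0.2; 3–5% | about +1; 5–6% |
| 6 variables, screened, same range (A at 5% only) | +0.6; 4.7% | +1.0 to +1.9; 5–7%, one run 8% |
| Longer list: 30 (A), 12–20 (B) | +1.2 to +4.5; 6–21% | about +1 to +5; 5–27% |

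The formula and the simulations agree where they overlap. Bias shrinks when the variables do predict replies, because less of the score is then noise.

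**After correction.** In Model A, with leave-one-out or split-sample scoring, the false difference lies between −0.4 and +0.4 points (Monte Carlo SE 0.13 to 0.17) and rejection is about 3–7%.

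**The case against.** The subgroup is defined by baseline traits held in both arms, so the same rule can be applied to controls and the randomised comparison is kept. Treatment outcome is not used to choose the traits. Literacy, education and age may well predict replying to a text message, and with six such variables the bias is small. If none of them predicts replies, the screen often finds nothing: 0.95⁶ = 0.74, so in about 74% of such trials no subgroup would be formed. With 15% false positives in the remaining 26%, the overall rate is about 0.26·0.15 = 4%. Cross-fitting, cut-off and interaction test are commonly left to the SAP, which is not shown. This is one of five subgroup analyses, and its hypothesis is worded tentatively.

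Most of this stands, and it limits the size of the point. It does not remove it. The Protocol states the screen, the single arm it uses and the analysis that follows, so this is a stated rule and not an omitted detail. When the screen does select useless variables, the reported contrast is biased in a known direction. The wording also leaves the list open, and the benign case depends on a short list of variables that truly predict replies.

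A reader might infer three stronger things that the text does not support:

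- **That patients are grouped by whether they actually replied.** This would be a far larger selection error, but the text looks for traits associated with replying and does not define the subgroup by replies.
- **That a third arm exists.** The Interactive Reminders arm can only be the Zindagi SMS arm, a two-way reminder system in a two-arm design. The name is a wording slip.
- **That a spurious benefit is certain.** It is possible, and its size depends on quantities that the Protocol does not give.

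**Conclusion.** The concern holds in a limited form: choosing reply predictors and examining the effect in the same SMS patients can bias the high-minus-low contrast towards greater benefit in likely responders.

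Under a true null with 1,094 per arm:

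- **Six variables that predict replies even modestly:** roughly 0 to +2 points, with about 3–7% false positives.
- **Six variables that do not predict replies:** about +1 to +3.5 points and 7–15%. Under the significance screen this applies to the trials in which some variable is selected.
- **12 to 30 variables:** about +1 to +5 points and 5–27%.

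For scale, the trial is sized for an overall difference of 5 points. These ranges rest on assumed links between replies and success, a linear score and a median split. The direction follows if replying goes with success, and the size is uncertain. The primary intention-to-treat comparison and the other four subgroup analyses are not affected. The change is worth making because it is cheap.

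**What to change.** Amend the last item under Sub-group Analysis as follows:

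1. Replace the open list and the significance screen with a closed, pre-listed set of baseline variables, all of which enter the score.
2. Score each SMS patient from a model fitted without that patient (leave-one-out, k-fold or split-sample), and score controls by the same procedure.
3. Test the treatment-by-score interaction across both arms and label the result exploratory.
4. As a wording correction only, use the Zindagi SMS arm's name throughout.

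The cost is a short change of text, a few lines of code and slightly noisier scores. No additional data are needed.
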